### Sample size and power analysis

The target sample size of 500 participants (250 per arm) was calculated based on the primary outcome of change in PTSD symptoms, as measured by the PCL-5. The sample size was determined to detect a minimum effect size (Cohen’s d) of 0.4, which represents a clinically meaningful difference in PTSD symptoms between the two intervention arms. This effect size is consistent with previous studies of psychosocial interventions for conflict-affected populations [46]. The power calculation assumed a two-sided significance level of 0.05, a power of 80%, and an intra cluster correlation coefficient (ICC) of 0.05 to account for the clustering of participants within IDP camps or communities. The ICC was estimated based on previous cluster-randomized trials of mental health interventions in humanitarian settings [47]. To account for potential attrition, the sample size was inflated by 15%, based on an anticipated dropout rate of 10–15% over the 12-week intervention period. This attrition rate is consistent with previous longitudinal studies of IDPs and takes into consideration the potential challenges of retention in the context of ongoing displacement and insecurity [48].

Based on these parameters, a total of 20 clusters (10 per arm) with an average of 25 participants per cluster (500 participants in total) will provide sufficient power to detect a clinically meaningful difference in PTSD symptoms between the in-person and mobile-delivered LSE interventions, while accounting for clustering and attrition.

### The adapted evidence-based intervention

The LSE intervention will consist of a culturally adapted curriculum covering core life skills topics such as stress management, communication, problem-solving, goal setting, health and hygiene, safety and protection, and social support. The curriculum will be developed through a participatory process involving IDP men and women, community leaders, mental health experts, and humanitarian actors, drawing on existing evidence-based resources, particularly the UNICEF Comprehensive life skills framework [49].

Agencies of the United Nations list the ten core life skill strategies and techniques as: problem solving, critical thinking, effective communication skills, decision-making, creative thinking, interpersonal relationship skills, self-awareness building skills, empathy, and coping with stress and emotions [50] (Fig. 2). These skills will be categorized into an initial group of skills that contribute to the four outcome areas of life-long learning, employability and entrepreneurship, personal empowerment, and active citizenship [51]. These transferable skills are building also helps prevent aggressive and conflict inducing behaviour later in life and is essential to any post-crisis reconciliation, social cohesion and longstanding peace [51].

**Fig. 2 Fig2:**
[figure not shown]
The life skills education scope

In the in-person arm, participants will attend weekly 120-minute peer support group sessions facilitated by trained IDP men and women and supervised by local mental health workers. The groups will be gender- and age-segregated (13–15, 16–19, and 18 + years) to create safe spaces for open discussion and skills practice. Sessions will employ interactive and experiential learning techniques such as role-plays, storytelling, games, and art-based activities to enhance engagement and retention.

In the mobile arm (i.e. WhatsApp), participants will join gender- and age-specific mobile groups moderated by trained facilitators. The groups will receive weekly LSE content and exercises through a combination of messages, voice notes, images, and live audio sessions. Participants will be encouraged to share reflections, ask questions, and provide peer support through the WhatsApp chat. Facilitators will stimulate discussion, offer feedback, and monitor participant safety and engagement.

Both arms will receive the LSE intervention for a duration of 12 weeks, with an average of 10–12 participants per peer support group. Fidelity to the intervention will be assessed through structured observations, attendance records, and facilitator logs [52]. Participants will receive the equivalent of $20 US and be provided with snacks during the intervention. Participants will also have access to referral information for additional mental health and social services as needed.

### Theory of change

The RESETTLE-IDPs study is guided by a theory of change that posits a pathway from the LSE intervention to improved mental health and well-being outcomes among IDPs (Fig. 3). The LSE intervention is hypothesized to lead to a series of proximal outcomes, including:

Increased knowledge and awareness of coping strategies.Enhanced problem-solving and decision-making skills.Improved communication and interpersonal skills.Increased emotion regulation and stress management abilities.Greater sense of self-efficacy and agency.Strengthened social support and connectedness.

**Fig. 3 Fig3:**
[figure not shown]
The RESETTLE-IDPs theory of change model

These proximal outcomes are expected to mediate the effect of the LSE intervention on the primary outcome of reduced PTSD symptoms, as well as the secondary outcomes of reduced depression and anxiety symptoms and improved well-being. The theory of change also recognizes the potential moderating effects of individual, social, and contextual factors on intervention effectiveness and implementation.

By articulating the hypothesized causal pathways and mechanisms of change, the theory of change provides a conceptual framework for designing the intervention, selecting measures, and analyzing results. It also helps to identify key constructs and processes to be assessed in the process evaluation to elucidate how and why the intervention works in this context. The theory of change will be refined based on study findings and stakeholder input to inform future implementations and adaptations of the LSE intervention for IDPs.

### Outcomes and measures

The study outcomes will be guided by the Reach-Effectiveness-Adoption-Implementation-Maintenance (RE-AIM) framework [53]. Reach will assess the number, proportion, and representativeness of IDP men and women participating in the LSE intervention. Effectiveness will evaluate the intervention’s impact on primary and secondary clinical health outcomes. Adoption will determine the uptake of the LSE intervention among IDP camps and humanitarian organizations. Implementation will examine the fidelity, consistency, and cost of delivering the intervention. Finally, maintenance will evaluate the long-term sustainability using camp reports and LSE intervention within organizational and state programs (Table 1). To maximize the program’s impact, we will assess both its clinical effectiveness and implementation processes. By comprehensively assessing these dimensions, we aim to optimize the intervention’s impact and inform future implementation efforts.

**Table 1 Tab1:** Outcome measures defined by the RE-AIM framework

RE-AIM Outcome	Operational Definition	Measures
**Reach**	The absolute number, proportion, and representativeness of IDP men and women who participate in the LSE intervention.	- Number and percentage of eligible participants who enroll in the study - Demographic and clinical characteristics of participants compared to the target population
**Effectiveness**	The impact of the LSE intervention on primary and secondary mental health outcomes among IDP youth and women.	- PTSD symptoms (PCL-5) - Depression symptoms (PHQ-9) - Anxiety symptoms (GAD-7) - Well-being (WHO-5) - Life skills acquisition (locally developed measure)
**Adoption**	The absolute number, proportion, and representativeness of IDP camps and humanitarian organizations that agree to deliver the LSE intervention.	- Number and percentage of IDP camps that participate in the study - Number and types of humanitarian organizations that support the intervention
**Implementation**	The fidelity, consistency, and cost of delivering the LSE intervention as intended in real-world IDP settings.	- Adherence to the LSE curriculum and delivery protocol (facilitator logs, observations) - Dosage of intervention received by participants (attendance records) - Quality of intervention delivery (participant ratings, facilitator competence) - Adaptations made to the intervention during implementation (facilitator logs, interviews)
**Maintenance**	The extent to which the LSE intervention becomes institutionalized or part of routine humanitarian programming for IDPs over time.	- Continuation of the LSE intervention beyond the study period (camp reports, observations) - Integration of the LSE intervention into existing humanitarian services (organizational policies, budgets) - Sustained effects of the intervention on mental health outcomes at 6 and 12-month follow-up (PCL-5, PHQ-9, GAD-7, WHO-5) - Perceptions of the intervention’s sustainability and scalability (stakeholder interviews)

Clinical outcomes will focus on primarily the intervention effectiveness in in changing PTSD symptoms from baseline to post-intervention (12 weeks), as measured by the Post-Traumatic Stress Disorder Checklist for DSM-5 (PCL-5) [54]. The PCL-5 is a 20-item self-report measure that assesses the presence and severity of PTSD symptoms on a 5-point Likert scale, with higher scores indicating greater symptom severity. The measure has been validated in several cultural contexts and shows good psychometric properties and will be validated to the local Hausa Language [55]. Secondary outcomes include changes in depression symptoms (Patient Health Questionnaire-9), anxiety symptoms (Generalized Anxiety Disorder-7), well-being (WHO-5), and life skills acquisition (locally developed measure) [56–58].

Implementation outcomes will assess the acceptability, appropriateness, fidelity, and feasibility of the intervention. To gain a deeper understanding of these factors, a qualitative process evaluation will be conducted throughout the study. This evaluation will explore factors influencing program delivery, participant experiences, and program outcomes, including barriers and facilitators to implementation. Data will be collected through in-depth interviews with program facilitators, key stakeholders, and participants, as well as focus group discussions and observations. By examining the intervention’s processes, we aim to inform post-project sustainability and scaling plans. Outcomes will be assessed at baseline, three months, and at the follow up periods of six months and 12-month follow-up by trained research assistants.

### Data collection and management

To gather in-depth data on the LSE intervention, we will employ a mixed-methods Quantitative data will be collected using a combination of interviewer-administered questionnaires and self-interviewing. Questionnaires will be translated and back-translated into Hausa and pilot-tested for comprehension and cultural appropriateness. Data will be entered into a secure, password-protected database using unique participant identification numbers to maintain confidentiality.

Qualitative data from participants, program facilitators and stakeholders will be collected through facilitator logs, in-depth interviews, focus group discussions, and participant observations by the research assistants. Interviews and discussions will be audio-recorded, following consent from participants and stored in secured system, transcribed verbatim, and translated into English by external vendors, for analysis. All transcribed, anonymized and translated interviews will be reviewed by the study team for accuracy before analysis. Field notes and memos will be used to capture contextual details and researcher reflections. Data quality will be ensured through regular monitoring, double data entry, and range and consistency checks.

### Data analysis

Implementation outcomes will be assessed using the Acceptability of Intervention Measure (AIM), Intervention Appropriateness Measure (IAM), Facilitator Fidelity logs, observation checklist of program implementation and observation of staff training on the life skills curriculum, and Feasibility of Intervention Measure (FIM) [59]. Cost-effectiveness will be calculated by estimating the total program costs and comparing them to the achieved health outcomes.

Qualitative data analysis will employ a reflexive thematic analysis approach using both inductive and deductive coding strategies to identify key themes related to implementation, acceptability, fidelity, and feasibility. Transcripts will be coded iteratively to identify emerging themes and patterns, with constant comparison within and across cases. Memos and matrices will be used to facilitate synthesis and interpretation. Triangulation of qualitative and quantitative findings will be performed to enhance validity and identify convergent and divergent results [60, 61].

Quantitative data analysis will follow an intention-to-treat approach, using mixed-effects linear regression models to assess intervention effects on primary and secondary outcomes. Models will include fixed effects for time, group assignment, and their interaction, and random effects for clusters and participants. Baseline characteristics will be included as covariates to adjust for potential confounding. missing data will be handled using list wise deletion (complete case analysis) or multiple imputation (MI) methods.

Effect sizes will be expressed using Cohen’s (standardized mean differences) with 95% confidence intervals. To account for potential biases from unmeasured confounders, propensity score matching will be employed to adjust the effect size estimates.

intervals. Subgroup analyses will explore differential effects by gender, age, displacement duration, and baseline symptom severity. Sensitivity analyses will be conducted to assess the robustness of the findings to different assumptions and methods.

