**Methods:**

This cluster-randomized hybrid type 2 effectiveness-implementation trial will be conducted in 20 IDP camps or host communities in Maiduguri, Nigeria. Sites will be randomly assigned to receive a 12-week LSE program delivered either through in-person peer support groups or WhatsApp-facilitated mobile groups. The study will recruit 500 participants aged 13 years and older. Intervention effectiveness outcomes include the primary outcome of change in post-traumatic stress disorder (PTSD) symptoms assessed using the PCL-5 scale, and secondary outcomes of depression, anxiety, well-being, and life skills acquisition. Implementation outcomes will be assessed using the Acceptability of Intervention Measure (AIM), Intervention Appropriateness Measure (IAM), and Feasibility of Intervention Measure (FIM). Both sets of outcomes will be compared between the in-person and mobile delivery groups. Quantitative data will be analyzed using mixed-effects linear regression models, while qualitative data will be examined through reflexive thematic analysis. The study will be guided by the Reach-Effectiveness-Adoption-Implementation-Maintenance (RE-AIM) framework.

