### Study setting and participants

The study will be conducted in IDP host communities in Maiduguri, the capital of Borno State in Northeast Nigeria. Since the emergence of the Boko Haram conflict in 2009, Maiduguri has become the hub of IDPs and hosts the highest proportion of IDPs in the country, 76%. An estimated 49% of these IDPs reside in 237 camp/camp-like settings, and 51% are in host communities [4]. The IDP host communities will be our unit of randomizing, using a computer generation. Selection criteria for our two study sites include population size, non-existence of MHPSS, network availability, and the presence of local partners and infrastructure to support the research.

The target population includes IDPs 13 years and older who have been displaced for at least three months. Participants will be recruited through a combination of purposive sampling strategies, with the assistance of camp leaders, community mobilizers, and humanitarian organizations in those sites, given the intervention delivery approach: in-person and mobile arm group. Inclusion criteria are: (1) resident in IDP camp for 6 months; (2) aged 18 years or older; (3) speaks English or Hausa; (4) having access to a mobile phone or being willing to share one (for the Mobile, i.e., WhatsApp, arm); and (5) providing informed consent/assent. It is important to note that while device sharing is allowed for participation in the Mobile arm, it may pose potential risks to participants’ privacy and confidentiality. Measures will be taken to mitigate these risks, such as providing guidance on secure device sharing practices and ensuring that shared devices have appropriate security features enabled.

Exclusion criteria include (1) the presence of mental illness, cognitive impairment, or substance abuse that would hinder meaningful participation following the baseline assessment; (2) imminent risk of suicide or violence requiring immediate referral; and (3) unwillingness to participate in the study or complete study assessments.

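### The one stated cost-effectiveness rule sets total programme cost against achieved outcomes and does not refer to the between-arm contrast, the only effect this trial randomises

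*Protocol article*

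**What the plan says.** Under Data analysis, the protocol article states: "Cost-effectiveness will be calculated by estimating the total program costs and comparing them to the achieved health outcomes". Under Outcomes and measures, it places cost within the RE-AIM dimensions: "Implementation will examine the fidelity, consistency, and cost of delivering the intervention". No other text describes an economic analysis. The sentence does not say whether costs are totalled by arm or over the whole programme, which outcome is meant, or that a difference between arms will be taken.

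The design is comparative. The abstract says of the effectiveness and implementation outcomes: "Both sets of outcomes will be compared between the in-person and mobile delivery groups". Both arms receive life skills education for 12 weeks, and no arm goes without it. The primary outcome is PCL-5 change from baseline to 12 weeks. The clinical models under Data analysis contain a group-by-time interaction, which is the between-arm contrast.

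Some costs are common to both arms. The section on the adapted intervention says, without distinguishing arms: "Participants will receive the equivalent of $20 US and be provided with snacks during the intervention".

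**The concern.** Randomisation here identifies one thing: the difference between in-person and mobile delivery. The outcome achieved within an arm also contains whatever improvement would have happened without the programme, and no untreated arm exists to remove it. Total cost likewise contains items that both arms carry equally. Dividing one by the other, or setting them side by side, gives a figure that moves with quantities unrelated to the choice of format. If costs are pooled over both arms, it gives no comparison at all.

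The Discussion expects the trial to inform scale-up of delivery models. A reader who takes the format with the lower cost per achieved point as the better buy could be misled. The clinical analysis already uses the right contrast, but the cost sentence does not refer to it.

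**Working it through.** The plan states no cost, no cost-effectiveness figure and no value per PCL-5 point, so there is no figure to reproduce. The checks below ask only whether the literal rule and an incremental analysis can disagree. All costs and effects are assumed, except the $20 payment in check 3.

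**Formulas.** For arm *a* with mean cost *C* and mean PCL-5 fall *E*:
- cost per achieved point = *C* / *E*;
- incremental ratio = (*C*_in-person − *C*_mobile) / (*E*_in-person − *E*_mobile);
- net benefit = λ*E* − *C*, where λ is the value of one point.

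**Check 1: shared improvement.** Assume costs of $120 (in person) and $60 (mobile), format-specific falls of 6 and 2 points, and a shared improvement of *u* points in both arms.

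| *u* | In person | Mobile | Lower cost per point | Incremental ratio |
|---|---|---|---|---|
| 0 | 120/6 = $20.00 | 60/2 = $30.00 | in person | 60/4 = $15 |
| 3 | 120/9 = $13.33 | 60/5 = $12.00 | mobile | $15 |
| 6 | 120/12 = $10.00 | 60/8 = $7.50 | mobile | $15 |
| 10 | 120/16 = $7.50 | 60/12 = $5.00 | mobile | $15 |

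The order changes where 120(2 + *u*) = 60(6 + *u*), that is 60*u* = 120, so *u* = 2 points. The randomised difference is the same in every row.

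**Check 2: does the ranking matter for the decision?** Take the row *u* = 6, with achieved falls of 12 and 8 points. Cost per point favours mobile. Net benefit depends on λ:
- λ = $10: in person 120 − 120 = 0; mobile 80 − 60 = 20. Mobile is better, so the two approaches agree.
- λ = $15: 180 − 120 = 60; 120 − 60 = 60. Equal.
- λ = $20: 240 − 120 = 120; 160 − 60 = 100. In person is better, so they disagree.

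In this row the literal rule misranks only if a point is worth more than $15.

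**Check 3: shared cost.** Assume costs of $80 and $20 before the participant payment, and falls of 6 and 2 points.
- Without the payment: 80/6 = $13.33 against 20/2 = $10.00, so mobile is lower.
- With the stated $20 in each arm: 100/6 = $16.67 against 40/2 = $20.00, so in person is lower.
- Incremental ratio: 60/4 = $15 both times.

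A payment identical in both arms can reverse the order.

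**Check 4: participant-borne costs.** Return to check 1, where the incremental ratio is $15. If mobile participants each bore an assumed $15, it would be (120 − 75)/4 = $11.25. If in-person participants bore the $15 instead, through travel or time, it would be (135 − 60)/4 = $18.75. The direction depends on which arm bears more, and the document does not say.

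**The case against.** The strongest reply is that the sentence names no ratio, no per-arm average and no ranking rule. An article condenses a fuller protocol, and an incremental analysis may be specified there. The abstract's statement that outcomes are compared between arms, and the interaction term in the clinical models, suggest that the authors think comparatively. Cost perspective, cost items and the uncertainty method are commonly left to a fuller plan.

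Much of this stands. The document cannot be said to prescribe an average ratio, and the absence of economic detail is not itself an error. What remains is narrower: the one rule that is written down sets total cost against achieved outcome, and taken as written it is not the comparison the trial can support.

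Three stronger readings are tempting but unsupported.
- *The plan will rank the formats wrongly.* That needs costs, effects and a value per point that the document does not give. Check 2 shows the rankings can also agree.
- *WhatsApp delivery shifts costs to participants, so a programme-cost view favours it.* Mobile participants need an owned or shared phone, but the article does not say who pays for data, airtime or charging; if the programme does, these are programme costs. In person, "participants will attend weekly 120-minute peer support group sessions facilitated by trained IDP men and women", which is 12 × 2 = 24 hours over 12 weeks if every weekly session is held, plus any travel. That burden also lies outside programme costs. No direction of bias is established, and a provider perspective is a legitimate choice.
- *Table 1 is wrong because its Implementation row lists no cost measure.* An article may leave that measure to a fuller plan.

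**Conclusion.** The point holds as a weakness in a stated secondary analysis. Read literally, the rule gives an uncontrolled cost per achieved outcome that includes improvement and costs common to both arms. It therefore does not show the relative value of in-person and mobile delivery.

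The possible size is a complete reversal of order, as in checks 1 and 3, against an unchanged incremental ratio of $15 per point. Those dollar figures illustrate the mechanism and do not estimate this trial's result. Whether a reversal would occur depends on the real costs, the real effects and the value placed on a PCL-5 point.

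Cost-effectiveness is not among the five numbered aims, and nothing here touches the primary analysis or the sample size. The change is worth making because it costs little and uses a contrast that the trial already estimates.

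**What to change.** Replace the sentence under Data analysis with wording such as: *Programme costs will be estimated separately for each arm. The difference in mean cost per participant, in-person minus mobile, will be set against the model-based difference in PCL-5 change at 12 weeks and reported as an incremental cost-effectiveness ratio or as net benefit over a stated range of values per point, with an interval that respects clustering.*

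Net benefit is the safer of the two summaries if the arms turn out similar, because the ratio is undefined when the effect difference is zero. The interval could come from a bootstrap that resamples whole clusters or from a bivariate model with cluster effects; with only 10 clusters per arm it should not treat participants as independent. State the cost perspective in the same sentence.

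Participant-borne costs in both arms (data, charging, travel, time) can be an optional sensitivity analysis, using two or three questions at the existing three-month assessment.

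The price is cost records kept by arm, slightly more analysis, and a headline less simple than one cost per point. No change to design, recruitment or sample size is needed.

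### If the stated random effects are intercepts, the group-by-time test of PCL-5 change omits the camp-level clustering in change that the sample size pays for

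*Protocol article*

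**What the plan says.** Three statements in the protocol article bear on this point.

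- **Analysis model** (Data analysis): "Models will include fixed effects for time, group assignment, and their interaction, and random effects for clusters and participants". Time is crossed with group among the fixed effects. Among the random effects time does not appear. The text does not say whether the random effects are intercepts, slopes or both.
- **Primary outcome** (Outcomes and measures): the effectiveness outcome is "changing PTSD symptoms from baseline to post-intervention (12 weeks), as measured by the Post-Traumatic Stress Disorder Checklist for DSM-5 (PCL-5"). Assessments are at baseline and 3, 6 and 12 months.
- **Sizing** (Sample size and power analysis): the sample size "was calculated based on the primary outcome of change in PTSD symptoms, as measured by the PCL-5", with a "minimum effect size (Cohen’s d) of 0.4", two-sided 5% significance, 80% power and an "intra cluster correlation coefficient (ICC) of 0.05 to account for the clustering of participants within IDP camps or communities". The design is 20 clusters, 10 per arm, averaging 25 participants, with 15% inflation for attrition.

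**The concern.** The outcome is a change from baseline, so in a model of repeated scores the treatment effect is the group-by-time contrast between baseline and 12 weeks. A random intercept is constant over visits. It describes how camps or people differ in level and says nothing about how they differ in change. With intercepts alone, the model looks adjusted for clustering, but its primary contrast is not.

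Clustering in change is plausible here. The intervention is delivered in groups, and the article itself describes ongoing displacement, insecurity and a volatile setting. Such influences act after baseline and can differ between camps. The article does not measure how strong they are.

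At stake are the standard error, confidence interval and p-value of the primary comparison, and the agreement between how the trial was sized and how it is analysed.

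**Working it through.** **Inputs from the sample size section.** d = 0.4; two-sided alpha 0.05; power 80%; ICC 0.05; 10 clusters per arm; m = 25 per cluster; 15% attrition, so 25 x 0.85 = 21.25 analysed per cluster.

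**1. Reproduce the stated sample size.**
- Individually randomised: 2 x (1.960 + 0.842)^2 / 0.4^2 = 98.1, so 99 per arm.
- Design effect: 1 + (25 - 1) x 0.05 = 2.2, and 99 x 2.2 = 217.8.
- Attrition: 217.8 x 1.15 = 251, or 217.8 / 0.85 = 257.

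The stated 250 per arm is recovered to within 3%. The design effect of 2.2 was therefore charged to an outcome that the article calls change.

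**2. What the model does with change, on the intercepts reading.** For participant j in cluster i at visit t:

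Y_ijt = fixed part + u_i + v_ij + e_ijt

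The change is Y_ij1 - Y_ij0 = fixed part + (e_ij1 - e_ij0). Both u_i and v_ij have gone. The model has no parameter through which two people in one camp can have correlated changes. In a balanced design its standard error for the interaction is the unclustered change-score standard error. A fitted mixed model with cluster and participant intercepts, on simulated data, confirmed this: 0.0963 against 0.0963.

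**3. Size of the error.** Let rho be the ICC of change. The true variance of the contrast exceeds the model variance by a factor of about DE = 1 + (m - 1) x rho, so

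type I error = 2 x Phi(-1.96 / sqrt(DE)).

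For rho = 0.05 and m = 21.25: DE = 1 + 20.25 x 0.05 = 2.0125; sqrt(DE) = 1.419; 1.96 / 1.419 = 1.38; type I error = 16.7%.

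| ICC of change | m = 21.25 | m = 25 |
|---|---|---|
| 0 | 5.0% | 5.0% |
| 0.01 | 7.4% | 7.8% |
| 0.02 | 9.8% | 10.7% |
| 0.05 | 16.7% | 18.6% |

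Simulation with 20 clusters and two or four visits, at rho = 0.05, gave 16% to 17% for 21 per cluster and 18% to 19% for 25. Fully fitted mixed models rejected in 231 of 1,459 runs (15.8%).

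**4. If 0.05 is the ICC of the score at one visit.** The ICC of change then depends on two figures the article does not give: the cluster autocorrelation c and the within-person correlation r.

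rho = 0.05(1 - c) / [0.05(1 - c) + 0.95(1 - r)]

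Assuming r between 0.4 and 0.7, and m of 21.25 to 25, type I error is 5% at c = 1.0, about 7% to 10% at c = 0.9, about 9% to 15% at c = 0.8, and about 15% to 25% at c = 0.5.

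**The case against.** A reader might infer that the protocol restricts the model to random intercepts and that the trial will run at a 17% false-positive rate. The document supports neither statement.

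- **Random-effects structure.** The article does not write *intercept* and does not exclude a cluster slope or cluster-by-time effect. A condensed article may leave that detail to the full plan. This stands as a limit on how firmly the point can be put. It does not remove the point, because the terms that are listed, fitted in the usual way, give a primary test without clustering in change.
- **Dependent variable.** If change itself is modelled at 3, 6 and 12 months, the cluster intercept is clustering in change and does not cancel from the 12-week group effect. Simulated at a change ICC of 0.05 with 21 per cluster, that model had a type I error of 6.1% (persistent camp effects) or 8.5% (camp effects independent at each visit) with a z test, and 4.5% or 6.5% with 18 degrees of freedom. The article does not rule this out and never names the interaction coefficient as the primary test. The reading fits the listed terms less well, however. With change as the outcome, the group-by-time term would contrast later visits with 12 weeks and would not carry the 12-week effect.
- **The ICC.** The value 0.05 is not labelled an ICC of change, although it enters a calculation on change. If it is the ICC of the score, the range in step 4 applies. If camp effects on the score are also fully stable over time, the test holds its 5%, but then the design effect of 2.2 does not belong to a change outcome. The sizing and the analysis still disagree.
- **Mechanism.** Peer groups of 10 to 12 sit below the camp, and the article does not say that facilitators are shared across a camp's groups. Camp-level correlation in change is plausible but not documented.

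**Conclusion.** The point holds in conditional form. With random intercepts on repeated PCL-5 scores, the group-by-time test carries no clustering in change, while the sample size charges a design effect of 2.2 for it. The standard error is then too small whenever camps differ in change. With the protocol's 0.05 taken as the ICC of change, it is too small by a factor of 1.42 with 21.25 per cluster, and type I error is about 17%, or about 19% with 25 per cluster.

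These figures rest on three assumptions that the article does not state outright: intercepts only, raw scores as the outcome, and an ICC of change of 0.05. They describe what the ordinary reading would produce and are not an established property of the trial. The wording should still be corrected before analysis, because its usual implementation can invalidate the primary inference and contradicts the basis on which the trial was sized.

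**What to change.** State the outcome scale and the random-effects structure, and adopt one of these as the primary analysis:

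- **Longitudinal model:** repeated PCL-5 scores, time as categorical, random effects for cluster, participant and cluster-by-time, with the baseline-to-12-week contrast between arms named as primary.
- **Single-visit model:** 12-week PCL-5 on arm and baseline PCL-5, with a random cluster intercept.

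In either case use REML with Kenward-Roger or Satterthwaite degrees of freedom, about 18 for 20 clusters in two arms. Say also whether the ICC of 0.05 refers to the score or to its change.

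The cost is one paragraph and no new data. The confidence interval will be wider than the one the intercepts-only model would print. The planned size roughly supports the corrected test. At 21.25 per cluster and a change ICC of 0.05, the standardised standard error is sqrt(2 x 2.0125 / 212.5) = 0.138, and 0.4 / 0.138 = 2.91. That gives about 83% power by the normal approximation and about 78% with a t test on 18 degrees of freedom.
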